**Figure 2 figure2:**
[figure not shown]
Flow of participants through the randomized control trial. EMPOWER = Enabling Mothers to Prevent Childhood Obesity Through Web-Based Education and Reciprocal Determinism, SCT = social cognitive theory.

#### Sample Size for Efficacy Trial

Based on previous studies, significance criteria for this investigation were set at an alpha of .05, a power at 80%, and an effect size at 0.20 [12,14,27]. We established the number of groups at 2 and the number of measurements at 3. Correlation between repeated measures was set at .05 and nonsphericity correction at 1. Inputting these criteria into G*Power resulted in a sample size of 42 [28]. To account for potential attrition, we inflated the sample size by 20%, resulting in a total sample size of 50 with 25 participants allocated to each group.

### Participant Enrollment

We selected mothers as the primary agents of change in this intervention [29-33]. Children ages 4 to 6 have been targeted for this study because this age range has been demonstrated to be a strong predictor of future health [30,34]. Eligibility to participate in the intervention will be limited to the following inclusion criteria: (1) mothers with (2) high-speed Internet access, (3) working email, and (4) at least one child in the age range of 4 to 6 years. Exclusion criteria will be (1) non-English-speaking mothers, (2) pregnant mothers, and mothers with (3) a child outside the age range of 4 to 6 years, (4) a child inside the age range of 4 to 6 years with a physical disability that would interfere with participating in daily moderate to vigorously intense physical activity, (5) a child with a medical condition associated with weight gain, (6) a child prescribed medication associated with weight gain, or (7) a child enrolled in an additional weight management program. We will seek and obtain university institutional review board approval before implementing the intervention. Eligible mothers will be required to provide consent prior to enrollment. Children will be required to provide oral assent prior to enrollment.

### Participant Recruitment

The intervention will target the general population in Cincinnati, Ohio, USA. We will recruit 50 families from 10 to 15 local childcare centers (preschools, daycares, and kindergartens) to participate in the investigation [15]. Childcare center recruitment will entail calling local childcare center managers and requesting their support for the initiative. Presentations will be made to the childcare center managers describing the benefits of the program. During the presentations, we will emphasize the childcare centers’ role as a community stakeholder to garner support. Participant recruitment activities will include delivering flyers and 15-minute presentations to potential recipients at the childcare centers.

### Random Assignment

Eligible, consenting participants will be randomly assigned to either the theory-based (experimental) or knowledge-based (control) arm of the trial. The participant assignment protocol will be based on block randomization (block size will remain confidential to maintain allocation blindness). Allocation of block assignment will be determined using random number generator computer software. Participants will not know to which cohort they have been assigned to improve external validity. However, as we will recruit participants within the same childcare facilities, it is possible there will be spillover effects between the intervention and control groups. For example, mothers in the intervention group may share what they are learning with mothers in the control group. To buffer this effect, we will ask participants not discuss intervention-based activities with others in the facility. Maintenance of confidentially will be evaluated through process evaluation at the beginning and end of the intervention.

### Process Evaluation

Process evaluation will occur concurrently with each module to assess program fidelity and dose. Process evaluation is akin to quality control, in which standardized methods are employed to ensure programming is delivered systematically to all participants. In the absence of process evaluation, researchers increase the risk of committing a type III error. From a quality control perspective, a type III error occurs when weak or null results occur due to inconsistent or inadequate intervention delivery. To reduce the risk of committing a type III error, the proposed intervention will incorporate several layers of implementation process evaluation:

Log-in codes and tracking data will be used to assess whether the website and subsequent module materials were accessed.Date and duration of activity will be logged to assess whether audiovisuals were viewed and adequate time was spent to complete each activity.Online, interactive worksheets and module quizzes will have forced-response validation to gauge transference of information.Reminder emails will be sent to assess promotion.At the completion of the intervention, respondents will be requested to complete an open-ended questionnaire regarding acceptability and perceived usefulness of the program. Additionally, data regarding maintenance of confidentiality will be collected.Participants who drop out of the program will be contacted and asked why they discontinued the intervention. To help control for attrition the sample size has been inflated by 20% above what was required by the study power analysis.

### Data Analysis

We will collect data for the intervention over three phases: phase 1 at baseline (week 0), phase 2 at posttest (week 4), and phase 3 at follow-up (week 8). At each phase of data collection, we will collect from both groups (1) measures of the four obesogenic protective factors, and (2) summated scores for the SCT constructs. SAS version 9.3 (SAS Institute, Cary, NC, USA) will be used to conduct statistical analyses of the intervention. Each of the outcome measures will be tested using PROC MIXED to analyze the data collected in the repeated-measures statistical design. The model will account for gender (male, female) as a potential covariate.

The null hypothesis for the time effect is that the means of the outcome measures at each of the three levels will be equal. If we find statistically significant differences, we will plot least square means and apply the Scheffé post hoc test. Normality of the distribution of outcome measures, homogeneity of variances, and the Mauchly test of sphericity will be used to test the assumptions of repeated-measures analysis of variance. Variables that are not normally distributed or that display variance heterogeneity will be transformed to obtain distributions that are closer to normality and variance homogeneity. The Huynh and Feldt adjustment to any *F*-distribution degrees of freedom will be applied if the covariances between the repeated measures being analyzed do not follow a spherical distribution.

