### Specific Aims

#### Specific Aim 1

The American Medical Association, in collaboration with 15 health care organizations, developed a series of recommendations for the prevention and treatment of child and adolescent obesity [23]. The key lifestyle behaviors identified by the committee will serve as the basis for the behavioral outcome measures of this study. The four obesogenic protective factors measured in the intervention will be the child’s (1) engagement in 60 minutes of moderate to vigorously intense physical activity each day, (2) consumption of 3 or more cups of fruits and vegetables each day, (3) replacement of sugar-sweetened beverages with sugar-free beverages, and (4) limitation of screen time (television/computer time) to no more than 2 hours per day.

Therefore, the first specific aim of this study is to compare the effects of the EMPOWER intervention (experimental) with an equivalent knowledge-based intervention (control) on the four identified obesogenic protective factors from baseline (week 0) to postintervention (week 4) and 1-month follow-up (week 8) in children ages 4 to 6 years as measured through a valid and reliable behavior log.

#### Specific Aim 2

SCT is a robust theoretical framework for eliciting behavior change [24]. SCT is based on the premise of reciprocal determinism, a causal model that posits that human functioning is the result of environmental, personal, and behavioral factors. SCT is rooted in human potential and emphasizes modeling, symbolizing, forethought, self-regulatory, and self-efficacy capabilities. The key constructs of SCT will serve as the theoretical outcome measures for the study. The five SCT constructs that will be operationalized for the EMPOWER program will be (1) environment, which comprises the external stimuli to which an individual is exposed, (2) expectations, which are the anticipations that an individual has about a specific outcome and the values the individual places on those outcomes, (3) emotional coping, which is an individual’s ability to control emotional and psychological states associated with acquisition of a new behavior, (4) self-control, which results from explicit and specific goal setting for accomplishing a behavior, and (5) self-efficacy, which results from confidence in personal capability to perform a behavior. 

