### Intervention Design and Sampling

#### Design

The proposed 8-week program will use a group randomized experimental design to test the efficacy of the protocol. Statistically, we will use a repeated-measures one-between-, one-within-participants design. The protocol will be delivered to two cohorts randomly assigned to receive either the theory-based (experimental) or knowledge-based (control) protocol (see Figure 2). The primary independent variable in the proposed study is the intervention. This is a fixed, categorical variable with two levels: EMPOWER intervention and knowledge-based intervention. The second independent variable in the study is time (within-participants effect). This is also a fixed, categorical variable with three levels: (1) baseline, (2) postintervention (at 4 weeks), and (3) 1-month follow-up (8 weeks after baseline). The outcome measures for comparison between the experimental and control groups are the four obesogenic protective factors and the five SCT constructs.

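### Scheffé is a needlessly conservative follow-up for the two week-specific comparisons in the aims; with three time levels, unadjusted contrasts after a significant 2-df F test hold the same error rate with more power

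*Protocol article*

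**What the plan says.** Specific Aim 1 compares the arms on the child behaviours "from baseline (week 0) to postintervention (week 4) and 1-month follow-up (week 8) in children ages 4 to 6 years"; Specific Aim 2 does the same for the maternal constructs. The Design section describes the layout: "Statistically, we will use a repeated-measures one-between-, one-within-participants design".

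The section Sample Size for Efficacy Trial gives the planning inputs. The error rates and effect are "significance criteria for this investigation were set at an alpha of .05, a power at 80%, and an effect size at 0.20". The layout entered is "We established the number of groups at 2 and the number of measurements at 3". For the dependence between waves it states: "Correlation between repeated measures was set at .05 and nonsphericity correction at 1". The result follows: "Inputting these criteria into G*Power resulted in a sample size of 42". For attrition, the authors write: "we inflated the sample size by 20%, resulting in a total sample size of 50 with 25 participants allocated to each group". The section does not say which repeated-measures F test was sized.

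The Data Analysis section fits each outcome with PROC MIXED and states one null hypothesis, for the time effect: equal means at the three time levels. The follow-up rule comes directly after it: "If we find statistically significant differences, we will plot least square means and apply the Scheffé post hoc test". No other follow-up procedure is named.

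**The concern.** The omnibus F test shows only that the three waves are not all alike. The aims ask about two particular changes, to week 4 and to week 8, so some follow-up is needed to locate an effect. The one named is built to protect all possible contrasts, and its critical value is correspondingly high. If a less demanding criterion gives the same error control for the comparisons of interest, Scheffé gives up power for nothing. In a trial of 42 to 50 mothers that loss matters, mainly for showing an effect at both visits or at the visit where the effect is smaller.

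**Working it through.** **Inputs.** From the sample-size section: alpha .05, f = 0.20 (read as Cohen's f, the G*Power convention), k = 2 groups, m = 3 measurements, epsilon 1, printed correlation .05, N = 42, enrolled 50. Assumed, because the article does not give it: the pattern of the effect over time. Compound symmetry is assumed throughout.

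**Step 1: reproduce the plan's 42.** For the within or within-between F test, λ = f²·N·m/(1 − ρ), df = (2, 2(N − 2)).
- ρ = .50, N = 42: λ = 0.04 × 42 × 3 / 0.50 = 10.08, df (2, 80), power 80.3%. The smallest even N reaching 80% is 42.
- ρ = .05, N = 42: λ = 5.04 / 0.95 = 5.31, power 51.3%. The N needed is 78.

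So 42 fits a 2-df omnibus test at ρ = .50 but not at the printed .05. That mismatch is a separate matter; both values are carried forward here.

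**Step 2: why Scheffé is not needed.** There are three pairwise contrasts among three levels. If any two of those null hypotheses are true, the third is true as well, and all levels are equal. Every intersection of pairwise nulls is therefore the global 2-df null. Testing that null at .05 first, and then each contrast at .05, is a closed test, with family-wise error at most .05 for that outcome. The argument holds equally for time means and for between-arm differences at the three times.

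**Step 3: critical values at N = 42, 80 error df.** Scheffé: √(2 × F.95(2,80)) = √(2 × 3.111) = 2.49. Closed procedure: |t| > 1.99, given a significant F.

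**Step 4: effect patterns.** For arm differences (0, d, d), f = d/√18, so d = 0.20 × √18 = 0.85 SD. A single change from baseline then carries the share s = (d²/2)/(2d²/3) = 0.75 of λ. For (0, d/2, d) or (0, d, d/2), the larger wave has s = 1 and the smaller s = 0.25.

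**Step 5: power per contrast.** Scheffé power is P[F′(1, df₂, sλ) > 2·F.95(2, df₂)]. Closed-procedure power was simulated (200,000 trials per row). The simulation also reproduced the Scheffé figures.

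| N | ρ | Contrast | Scheffé | Closed |
|---|---|---|---|---|
| 42 | .50 | either visit, equal effect | 60% | 73% |
| 42 | .05 | either visit, equal effect | 31% | 42% |
| 42 | .50 | larger wave, effect halves or doubles | 75% | 80% |
| 42 | .50 | smaller wave, effect halves or doubles | 19% | 34% |
| 50 | .50 | either visit, equal effect, no loss | 70% | 81% |
| 50 | .05 | either visit, equal effect, no loss | 38% | 50% |

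**Step 6: joint outcomes at N = 42, ρ = .50.** With an equal effect, both visits are declared in 44% of trials with Scheffé and 65% with the closed procedure. A significant F with neither visit declared under Scheffé occurs in about 4% of trials when the effect is equal, halves or doubles. If only week 4 is affected it occurs in about 19%, against 6% with the closed procedure.

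**The case against.** Four things can be said for the plan.

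First, the Scheffé sentence follows a hypothesis about time. No group-by-time hypothesis is attached to it, so reading the between-arm comparisons from Scheffé tests is an inference. This stands, and the power figures above are conditional on it. The closed-testing argument does not depend on it: for pooled time means, too, Scheffé is stricter than three levels require.

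Second, Scheffé after a significant F is valid and controls error, so preferring another criterion is advice on efficiency. This also stands and keeps the point minor. But the procedure is a stated choice, not a detail left open.

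Third, the usual harm, a significant F with nothing located, is rare for sustained or graded effects. True. The larger loss is in declaring both visits, or the smaller one.

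Fourth, a reader might infer that the trial has 60% power where it promises 80%. The article does not support that. It promises 80% for one calculation and for no single contrast. The 60% needs ρ = .50, which is not the printed value, and an effect pattern the article does not give; at ρ = .50 the Scheffé figure runs from about 19% to 75%. The closed procedure does not reach 80% for an equal effect at N = 42 either: of the roughly 20 points between 80% and 60%, about 7 come from testing one contrast and about 13 from Scheffé. Nor does the text propose Scheffé over all six group-by-time means.

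**Conclusion.** The point holds as a minor, cheap improvement. Scheffé is stricter than three time levels require, and replacing it costs nothing in per-outcome family-wise error for the named comparisons. If it would be used for the between-arm changes, the gain at N = 42, f = 0.20 with an equal effect is about 12 to 13 percentage points per contrast at ρ = .50 and about 11 at ρ = .05. With an effect that halves or doubles between waves, at ρ = .50, it is about 5 points for the larger wave and 15 for the smaller. The logical argument is firm. The sizes rest on compound symmetry, f read as Cohen's f, and the stated patterns. Nothing here shows that the sample-size figure is wrong because of Scheffé.

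**What to change.** In Data Analysis, replace the Scheffé sentence with wording such as:

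> If the 2-df group-by-time test is significant at .05, the pre-specified contrasts (between-arm difference in change from baseline to week 4 and from baseline to week 8) are each tested at .05; with three time levels this closed procedure keeps the family-wise error at .05 for each outcome.

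In Sample Size for Efficacy Trial, add that the power refers to the 2-df omnibus test and not to each week-specific contrast.

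The cost is two sentences, with no added participants or data. What is given up is simultaneous coverage of unplanned contrasts, and the aims name none.

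### The Mauchly test and Huynh-Feldt adjustment do not fit the PROC MIXED analysis that the plan names for every outcome

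*Protocol article*

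**What the plan says.** All of the analysis text is in the Data Analysis section of the protocol article. It names one procedure: "Each of the outcome measures will be tested using PROC MIXED to analyze the data collected in the repeated-measures statistical design". The next paragraph turns to ANOVA: "the Mauchly test of sphericity will be used to test the assumptions of repeated-measures analysis of variance". A remedy follows, a Huynh-Feldt "adjustment to any *F*-distribution degrees of freedom will be applied if the covariances between the repeated measures being analyzed do not follow a spherical distribution". The same paragraph looks at the normality of the outcome measures and the homogeneity of their variances, and says: "Variables that are not normally distributed or that display variance heterogeneity will be transformed".

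Two other sections use the same ANOVA framing. Under Design, "we will use a repeated-measures one-between-, one-within-participants design". Under Sample Size for Efficacy Trial, the nonsphericity correction is set to 1, so sphericity is assumed. That section raises the total from 42 to 50, an inflation of 20% for possible attrition, and Process Evaluation repeats the allowance.

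**The concern.** PROC MIXED estimates a covariance matrix for the three visits by likelihood. It deals with non-sphericity through the covariance structure chosen and the denominator degrees of freedom. The Mauchly test and the Huynh-Feldt epsilon belong to the univariate repeated-measures ANOVA F ratio, computed on participants with every visit observed. The paragraph therefore prescribes checks and a remedy that cannot be applied to the F test it names.

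An analyst has two ways out. One is to run a separate repeated-measures ANOVA to obtain the Mauchly test and epsilon; in its standard form this drops any mother who misses a visit. The other is to stay in PROC MIXED and ignore the rule; if sphericity is assumed there, nothing protects the error rate. The two routes differ most when visits are missing, which the plan allows for.

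A smaller matter sits in the same paragraph. The model's normality and variance assumptions concern residuals, not the raw distribution of an outcome. A transformation triggered by the raw distribution also moves the estimates away from minutes, servings and construct scores, the units in which the aims are stated.

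**Working it through.** **1. The plan's own sample size.** Inputs from Sample Size for Efficacy Trial: "significance criteria for this investigation were set at an alpha of .05, a power at 80%, and an effect size at 0.20" and "We established the number of groups at 2 and the number of measurements at 3", with epsilon = 1. For the group-by-time test:

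- λ = f²·N·m·ε/(1 − ρ), df1 = (k − 1)(m − 1)ε, df2 = (N − k)(m − 1)ε, with f = 0.20, k = 2, m = 3.
- Printed correlation .05, N = 42: λ = 0.04 × 42 × 3/0.95 = 5.31, power 51.3%; 80% power would need N = 78. The stated 42 is not reproduced.
- Correlation .5, N = 42: λ = 0.04 × 42 × 3/0.5 = 10.08 on 2 and 80 df, power 80.3%. This gives exactly 42.

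The printed .05 is a separate matter. Correlation .5 is used below as an assumption because it returns the plan's figure.

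**2. Power with completers only.** 42 × 1.2 = 50.4, stated as 50. Losing 20% of 50 leaves 50 × 0.8 = 40.

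- 40 completers: λ = 0.04 × 40 × 3/0.5 = 9.6 on 2 and 76 df, power 78.2%.
- All 50 complete: λ = 12.0 on 2 and 96 df, power 87.3%.

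The difference, 87.3 − 78.2 = 9.1 points, is an upper limit on what a likelihood analysis could recover. Mothers with missing visits contribute only part of their information.

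**3. Type I error of the group-by-time test.** Simulation under the null, 40,000 replicates, 20 per arm, complete data. The covariance matrices are assumed, since the article gives none. Epsilon = [tr A]²/(2·tr A²), where A is the covariance matrix of the two orthonormal time contrasts. Example, AR(1) with correlation .7: A11 = .30, A22 = .44, A12 = .121, so epsilon = .5476/(2 × .313) = .875. The two-step column applies Huynh-Feldt within ANOVA only if Mauchly rejects at 5%. The unstructured column is the multivariate test, which leaves the covariance free.

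| Epsilon | Sphericity assumed, no correction | Two-step rule in ANOVA | Unstructured | Mauchly rejects |
|---|---|---|---|---|
| 1.00 | 4.9% | 4.9% | 4.9% | 5% |
| .875 | 5.5% | 5.1% | 4.9% | 56% |
| .81 | 5.9% | 5.1% | 5.0% | 83% |
| .67 | 7.1% | 5.3% | 5.0% | 99.8% |

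Mauchly often misses mild departures, but these cost little, and it nearly always finds the severe one.

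**4. Possible bias from dropping incomplete cases.** None of these inputs is in the article. Assume a true effect on change of 0.85 SD at both follow-up visits, correlation .50, and 20% overall dropout after week 4 that depends on the week-4 change (logistic slopes 1 and 2).

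- Complete-case estimate, week 4: about 0.75 and 0.65 SD.
- Complete-case estimate, week 8: about 0.80 and 0.75 SD.
- Likelihood estimate, week 8: about 0.85 SD at both slopes.

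This mechanism implies unequal dropout: about 26% control against 14% experimental at slope 1, and 29% against 11.5% at slope 2. If dropout is random or depends only on baseline, the complete-case change estimate stays at 0.85. The plausible range therefore runs from no bias to the figures above.

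**The case against.** A reader might infer that the plan commits to a complete-case analysis, or that a pre-test picks between two models once the data are in. The text supports neither. It never mentions complete cases, the exclusion of mothers with a missing visit, or a second procedure. The sphericity rule is written in advance, and what it alters is the degrees of freedom. Mauchly could even be run only as a diagnostic beside PROC MIXED.

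A reader might also infer that the pre-test rule inflates type I error. It does not to any important degree: applied within ANOVA it stays between 4.9% and 5.3%. The larger figures describe sphericity assumed with no correction. The bias figures rest wholly on assumed parameters, and the article allows for attrition without predicting it.

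Finally, covariance structure and missing-data handling are commonly left to an analysis plan that is not shown, so their absence from a condensed article is no fault. Normality of outcome measures is also common shorthand for normality of residuals.

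All of this stands, and it limits the size of the point. It does not remove the mismatch: the article goes beyond leaving detail open and fixes a test and a correction that its named model cannot use. The SAS covariance option TYPE=HF does not close the gap, because it imposes sphericity on the covariance matrix and does not correct degrees of freedom.

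**Conclusion.** The point holds as a mismatch between the stated rule and the stated model, and it should be corrected. A completer-only ANOVA is a probable consequence of carrying out the written steps, not something the text prescribes.

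The size depends on the route taken. In ANOVA with the correction, error control is sound, but observed data are discarded: power is 78.2% with 40 completers, assuming correlation .5 and 20% loss, and bias is possible if dropout depends on week-4 change. In PROC MIXED with sphericity assumed, type I error could reach about 5.5% to 7.1% for epsilon .875 to .67 under the covariance patterns assumed. The direction of the bias follows from the assumed dropout mechanism; its size cannot be fixed from the document. The point about residuals and transformation is secondary, and no harm from it has been quantified.

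**What to change.** Delete the Mauchly test and the Huynh-Feldt rule from Data Analysis. In their place, specify for each outcome PROC MIXED with an unstructured covariance matrix over the three visits (TYPE=UN), Kenward-Roger degrees of freedom, and all randomised mothers with available data.

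Assess normality and variance on the model residuals. Keep the main estimates on each outcome's original scale (minutes, servings or summated construct score), and report any transformed fit as a sensitivity analysis.

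The cost is wording only: no extra participants, visits or data. Three visits give 3 × 4/2 = 6 covariance parameters, which is manageable with 40 to 50 mothers.
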